## Abstract

**Background:**

Virtual reality (VR) has emerged as a promising technology for enhancing the health care of older individuals, particularly in the domains of cognition, physical activity, and social engagement. However, existing VR products and services have limited availability and affordability; hence, there is a need for a scientifically validated and personalized VR service to be used by older adults in their homes, which can improve their overall physical, cognitive, and social well-being.

**Objective:**

The main purpose of the CoSoPhy FX (Cognitive, Social, and Physical Effects) study was to analyze the effects of a VR-based digital therapeutics app on the cognitive, social, and physical performance abilities of healthy (high-functioning) older adults. This paper presents the study protocol and the results from the recruitment phase.

**Methods:**

A group of 188 healthy older adults aged 65-85 years, recruited at the Medical University of Lodz, Poland, were randomly allocated to the experimental group (VR dual-task training program) or to the control group (using a VR headset app showing nature videos). A total of 3 cognitive exercises were performed in various 360° nature environments delivered via a VR head-mounted display; the participants listened to their preferred music genre. Each patient received 3 sessions of 12 minutes per week for 12 weeks, totaling a minimum of 36 sessions per participant. Attention and working memory (Central Nervous System Vital Signs computerized cognitive battery) were used as primary outcomes, while other cognitive domains in the Central Nervous System Vital Signs battery, quality of life (World Health Organization–5 Well-Being Index), health-related quality of life (EQ-5D-5L), and anxiety (General Anxiety Disorder 7-item questionnaire) were the secondary outcomes. The group-by-time interaction was determined using linear mixed models with participants’ individual slopes.

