### Experimental Hypotheses

It is expected that significant relationships will be found between the 2 factors (group × time) for each of the tested cognitive, physical, and social performance scores. Specifically, cognitive, social, and physical performance scores are expected to significantly improve throughout the VR training intervention compared with the start, but only for the experimental group. No such change is expected to be observed for the control group.

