### Outcome Measures

Neuropsychological assessment was performed at baseline and after the intervention. The primary outcomes of the initial study comprised the cognitive, social, and physical performance abilities of healthy (high-functioning) older adults. The parameters that were selected are (1) a wide range of cognitive domains: composite memory, verbal memory, visual memory, psychomotor speed, reaction time, complex attention, cognitive flexibility, processing speed, executive function, simple attention, and motor speed (Central Nervous System Vital Signs [CNS-VS] battery) [31]; (2) physical performance across 6 subcomponents: lower body strength, upper body strength, aerobic endurance, lower body flexibility, upper body flexibility, and dynamic balance or agility (Senior Fitness Test); (3) standard grip strength (using a dynamometer); (4) the sense of loneliness (De Jong Gierveld Loneliness Short Form); (5) the quality of life and perceived well-being (World Health Organization [WHO]–5 Well-Being Index); (6) the health-related quality of life (EQ-5D-5L); (7) satisfaction with participation in social roles and ability to participate in social roles and activities (Patient-Reported Outcomes Measurement Information System Short Form 8a); and (8) the severity of anxiety symptoms (General Anxiety Disorder 7-item questionnaire [GAD-7]) [32].

The CNS-VS is a computerized neurocognitive test battery developed as a routine clinical screening instrument. It comprises 7 tests—verbal and visual memory, finger tapping, symbol digit coding, the Stroop Test, a test of shifting attention, and the continuous performance test. The result includes neurocognitive clinical evaluation domains—composite memory, verbal memory, visual memory, psychomotor speed, reaction time, complex attention, cognitive flexibility, processing speed, executive function, simple attention, and motor speed [31]. The CNS-VS clinical battery is sensitive to subtle cognitive deficits and progressive decline or improvement. Previous research has shown it is validated, reliable, and easy to use [33].

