### Statistical Methodology

An a priori computation of the required sample size based on the type of test, the expected effect size, the type I and type II error rates, the number of groups, and the number of measurements were performed according to Lu et al [41]. The statistical power analysis was conducted for a mixed model of repeated measures for 2 groups, 1 measure at a time (corresponding to the main cognitive performance scores detailed) with a 0.7 pre-post correlation, a 20% dropout rate, a medium effect size (0.5), a significance level of α=.05, and a statistical power of 1–β=.80. The necessary sample size for these parameters was 77 (n=154) participants per group.

The MUL stored the personal data of the interested and eligible participants on an internal cloud service, protected from external access. The data set for statistical analysis was fully anonymized. All data storage and processing comply with the General Data Protection Regulation (GDPR) and other applicable regulations. Where possible, fully anonymized data may be made publicly available through open-access repositories supporting the Open Science Initiative.

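### The abstract's mixed model has participant-specific slopes that two visits cannot separate from residual error; drop the slope term and name one two-visit model (the group-by-time estimate itself is unaffected)

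*Protocol article*

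**What the plan says.** The only description of the analysis model in the protocol article is in the abstract, under Methods: "The group-by-time interaction was determined using linear mixed models with participants’ individual slopes". It gives no random intercept, residual or covariance structure.

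Outcome Measures sets the schedule: "Neuropsychological assessment was performed at baseline and after the intervention". No intermediate cognitive assessment is described. The web platform mentioned in the Intervention section tracks compliance and performance in training, not the trial outcomes.

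Statistical Methodology describes the model used for the power calculation as a "mixed model of repeated measures for 2 groups, 1 measure at a time", "with a 0.7 pre-post correlation, a 20% dropout rate". It does not mention slopes. Experimental Hypotheses makes the group-by-time interaction the target of inference, and Challenges names attention and working memory as the primary outcomes from version 2.0 onwards.

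**The concern.** A random slope describes how participants differ in their rate of change. To estimate the spread of those slopes apart from measurement error, at least some participants need more than two time points, or repeat readings within a visit. Neither is described here. The abstract therefore names a random-effects structure that the visit schedule cannot support, and it differs from the two-visit model in the Statistical Methodology section.

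What is at stake is a clear and reproducible statement of the primary model. An analyst who follows the abstract will meet a refusal, a convergence problem or an arbitrary set of variance components. The analyst must then simplify in a way that the article does not specify, at a stage when it reports that the data are already being analysed.

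**Working it through.** **Inputs.** Two visits (Outcome Measures). Pre-post correlation r = 0.7, 20% dropout, effect 0.5 SD, "a significance level of α=.05, and a statistical power of 1–β=.80" (Statistical Methodology). Completers: 68 experimental and 62 control, no missing data reported (Participant Flow). Assumptions of mine: two-sided alpha, unit variance at both visits, time coded 0/1, and one score per visit for each outcome. The phrase on one measure at a time may mean one outcome per analysis, but no repeat readings within a visit are described in either case.

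**The plan's own figure.** The stated requirement is 77 per group.
- Two-sample t-test at 0.5 SD: 64 per group, and 64 × 1.2 = 76.8, rounded up to 77.
- Normal approximation: 63 per group, and 63/0.8 = 78.75, so 79.
- Two-visit repeated-measures formula with 80% retention and r = 0.7: 70.8, so 71. It gives 77.1 only at r = 0.3.

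The figure is thus reproduced by a calculation that does not use the 0.7. That is conservative and does not bear on the point here.

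**Identifiability.** Let a be the intercept variance, c the intercept-slope covariance, b the slope variance and s the residual variance. Then
- baseline variance = a + s
- pre-post covariance = a + c
- post variance = a + 2c + b + s

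That is three equations in four unknowns; the mapping has rank 3. Setting the left-hand sides to 1, 0.7 and 1 gives a = 1 − s, c = s − 0.3, b = 0.60 − 2s. Every s from 0 to 0.30 is admissible, and b runs from 0.60 to 0. In terms of counts, 130 completers give 130 × 2 = 260 observations for 260 random effects.

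**What stays identified.** The variance of a participant's change is b + 2s = (0.60 − 2s) + 2s = 0.60 for every s. The group-by-time contrast depends on this variance and not on how it is split.

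A check on one simulated data set (62 and 68 participants, r = 0.7, true effect 0.5 SD) agrees:

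| Residual variance | Slope variance | Log-likelihood | Group-by-time | SE |
|---|---|---|---|---|
| 0.05 | 0.431 | −298.266181 | 0.53702 | 0.12798 |
| 0.10 | 0.331 | −298.266181 | 0.53702 | 0.12798 |
| 0.15 | 0.231 | −298.266181 | 0.53702 | 0.12798 |
| 0.20 | 0.131 | −298.266181 | 0.53702 | 0.12798 |
| 0.25 | 0.031 | −298.266181 | 0.53702 | 0.12798 |

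The simple difference in mean change and a random-intercept-only model gave the same estimate and SE. One standard package fitted the full intercept-and-slope model without a warning and reported a residual variance of 0.233 and a slope variance of 0.066. Since 0.066 + 2 × 0.233 = 0.532, against 0.431 + 2 × 0.05 = 0.531 in the table, this is, within rounding, one arbitrary point on the same flat ridge.

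**Gain from baseline adjustment.** Change-score variance is 2(1 − 0.7) = 0.60. Baseline-adjusted variance is 1 − 0.7² = 0.51. The reduction is 1 − 0.51/0.60 = 15%, worth about 1/0.85 − 1 = 18% more participants. With 1/68 + 1/62 = 0.030835 and (1.960 + 0.842)² = 7.849:
- change score: detectable effect = √(7.849 × 0.60 × 0.030835) = 0.38 SD; power at 0.5 SD is 95.7%
- baseline-adjusted: √(7.849 × 0.51 × 0.030835) = 0.35 SD; power at 0.5 SD is 97.9%

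The variance ratio in general is (1 − r²)/(2(1 − r)) = (1 + r)/2, so the saving depends on r: 35% at 0.3, 25% at 0.5, 15% at 0.7, 5% at 0.9. In the simulated data, ANCOVA gave 0.488 (SE 0.113).

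**The case against.** The strongest reply is that nothing of inferential weight is wrong. The slope wording is one sentence in an abstract, the covariance structure is the kind of detail an analysis plan would carry, and the Statistical Methodology section already describes an estimable two-visit model. For completers, removing the slope, using a random intercept or using an unstructured covariance all give the same interaction estimate and SE. Most of this stands. It does not excuse the sentence, because the abstract positively names a term that the schedule cannot support and that the methods section does not contain.

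A reader might go further and infer that the primary test is invalid, or that the treatment effect itself is not identifiable. The documents do not support that: only the split between slope and residual variance is undetermined. A reader might also infer that a baseline-adjusted model must replace the group-by-time test. That does not follow either. Deleting the slope term is enough, and power at the planned effect is above 95% both ways. Baseline adjustment can also move the estimate (0.537 to 0.488 in the simulated data), so adopting it after results by arm are known would itself be a change of analysis.

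Finally, the phrase could be read as slopes without a random intercept. That model is identifiable, but with time coded 0/1 it forces a pre-post correlation of zero, against the 0.7 in the power calculation. Nothing suggests that it was intended.

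**Conclusion.** The point holds in limited form. If the abstract's model includes a random intercept and a residual, it is over-parameterised by one covariance parameter for a two-visit design, and it does not match the Statistical Methodology section. The effect is on the variance components and on whether the model will run. The group-by-time estimate and its SE are unaffected, given 130 completers with complete data. If participants with a baseline score only were included, the candidate covariance structures could give slightly different answers, and degrees of freedom may depend on the software; the article gives no basis for sizing either.

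The advantage of baseline adjustment is separate from the error and modest: 15% less variance, resting on the assumed correlation of 0.7 and equal variances at the two visits.

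**What to change.** Delete the individual-slopes term. State one two-visit model for each primary outcome, with either an unstructured 2x2 covariance and no separate residual or a random intercept only, and make the abstract agree with the Statistical Methodology section.

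As an improvement, estimate the treatment effect with adjustment for the baseline score, by ANCOVA or by a constrained longitudinal model with a common baseline mean. The two agree closely but not exactly. Adding age, sex and educational level, which are already collected at screening, is optional and not part of the error.

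Fix and date the choice before results by arm are seen. If they have been seen, report the choice as a change and show the group-by-time result beside it.

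The cost is one sentence and a small change of model code. No new data are needed and the sample size does not rise. At r = 0.7, the change-score test needs 2 × 7.849 × 0.60/0.25 = 37.7, so 38 per group, and the baseline-adjusted test 2 × 7.849 × 0.51/0.25 = 32.02, so 33. With 20% dropout these become 48 and 42, against the stated 77.

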**Results:**

In total, 122 (39%) of the initial 310 participants failed to meet the inclusion criteria, resulting in a recruitment rate of 61% (188/310). Among the participants, 68 successfully completed the intervention and 62 completed the control treatment. The data are currently being analyzed, and we plan to publish the results by the end of September 2024.

**Conclusions:**

VR interventions have significant potential among healthy older individuals. VR can address various aspects of well-being by stimulating cognitive functions, promoting physical activity, and facilitating social interaction. However, challenges such as physical discomfort, technology acceptance, safety concerns, and cost must be considered when implementing them for older adults. Further research is needed to determine the long-term effects of VR-based interventions, optimal intervention designs, and the specific populations that would benefit most.

**Trial Registration:**

ClinicalTrials.gov NCT05369897; https://clinicaltrials.gov/study/NCT05369897

**International Registered Report Identifier (IRRID):**

DERR1-10.2196/53261

## Introduction

### Background or Aims

The global demographic shift toward an aging population presents a pressing need to enhance the quality and effectiveness of health care [1]. Aging is typically associated with cognitive inactivity and, thus, cognitive impairment, resulting in escalating care demands and health care costs [2] and reducing daily functioning and quality of life among older adults [3]. As such, there is a need for effective interventions aimed at enhancing cognitive functions, which can mitigate their decline and promote healthy aging [4].

A promising tool with significant potential across various fields is virtual reality (VR), which has been found to be effective in caring for older individuals, both with and without cognitive impairment [5]. By offering immersive digital experiences, VR can provide varying levels of immersion and high immersion can be provided by head-mounted displays (HMDs), which can stimulate multiple sensory modalities [6]. Such heightened immersion enhances the sense of presence, yielding more pronounced behavioral responses [7].

In addition to the general cognitive function, VR-based training programs have shown promise in improving specific cognitive domains, such as short-term memory, orientation, attention, comprehension, naming, constructions, memory, and judgment [8]. Indeed, VR interventions have been found to significantly improve executive function and verbal memory in older adults [9], whereas traditional cognitive training methods may be limited in terms of accessibility, motivation, and ecological validity [10]. VR technology offers a unique opportunity to create immersive and engaging 3D experiences that simulate real-world scenarios and involve multiple sensory modalities [11,12]. Indeed, studies indicate that VR interventions can enhance the effectiveness and engagement of cognitive interventions, resulting in better outcomes among older patients [13]. VR-based training may also have a beneficial influence on physical activity, with research suggesting it can improve balance performance and functional mobility [14]. Additionally, the potential of VR interventions to promote social engagement and combat social isolation has also been studied among older adults [15].

Research has shown that music has many positive effects on human health, including reducing stress and anxiety [16], enhancing mood [7], improving sleep [17], and relieving pain [18], and it can be an excellent motivator for physical activity [19]. Music has previously been integrated into VR experiences among older adults [11] to increase motivation [11], improve mental well-being [20], and support rehabilitation [21].

While studies have examined the use of VR in health care settings, particularly in mental health [22], its application in healthy older adults who can use VR at home is still an emerging area of research [11]. Understanding the benefits and potential limitations of home-based VR interventions is crucial for developing evidence-based strategies to support healthy aging [4]. Further research is still needed to assess the impact of VR interventions on specific cognitive, physical, and social domains and to identify the optimal protocols for therapeutic use.

Currently, existing VR products and services are prohibitively expensive for many home end users, and their use is typically limited to clinics, nursing homes, and rehabilitation centers [23]. However, the most effective strategy for ensuring maintainable health care in the face of aging populations is prevention. As such, there is a need to provide a home-based service that offers scientifically validated, safe, engaging, and personalized content for older adults to enhance their cognitive, physical, and social abilities.

### Objective

The main aim of the study is to determine the effects of using a VR-based digital therapeutics app to improve the cognitive, social, and physical performance abilities of healthy (high-functioning) older adults.

### Experimental Hypotheses

It is expected that significant relationships will be found between the 2 factors (group × time) for each of the tested cognitive, physical, and social performance scores. Specifically, cognitive, social, and physical performance scores are expected to significantly improve throughout the VR training intervention compared with the start, but only for the experimental group. No such change is expected to be observed for the control group.

## Methods

### Trial Design

The Cognitive, Social, and Physical Effects (CoSoPhy FX) study was designed as a randomized, parallel-group, 2-arm, superiority study with an aimed 1:1 allocation ratio. The protocol was registered with ClinicalTrials.gov (NCT05369897) on June 30, 2022.

### Participants

#### Recruitment

In total, 200 high-functioning older adults aged 65-85 years from a community-dwelling setting were recruited for the study. All recruitment was performed by the Medical University of Lodz (MUL), Poland. High-functioning older adults were defined as those who were older than 65 years of age and maintained their functional independence concerning activities of daily living, including the ability to go on a long walk and to interact with standard modern technology (eg, using a smartphone to send a message).

The recruitment strategy included the following: (1) promotional materials such as posters, flyers, press announcements, and posts on social media groups devoted to older adults were used to raise awareness in the local community and inform older adults about the project; (2) a dedicated phone line operating during working hours was set up to answer inquiries regarding participation in the study; and (3) study visits were carefully planned and scheduled to work around holiday breaks.

The enrollment period lasted over 12 months. The allocated research team member screened the potential participants according to the eligibility criteria, given in Textbox 1.

Inclusion and exclusion criteria.
**Inclusion criteria**
Individuals aged 65-85 yearsStable medical condition (eg, well-controlled diabetes or hypertension)Undisturbed locomotionIndependent in everyday functioningCapable of going on long walks without assistanceAble to use standard modern technology
**Exclusion criteria**
Neuropsychiatric disorders (Montreal Cognitive Assessment<26 points)Abuse or addiction to alcohol, drugs, and tranquilizers (*Diagnostic and Statistical Manual of Mental Disorders, Fifth Edition*)Blurred vision that cannot be corrected with lenses or glassesAuditory pathologies causing significant hearing lossHigh sensitivity to motion sicknessMigrainesEpilepsyObesity (BMI>30)Deemed unsuitable for participation by the investigator

The clinical and demographic data that were collected during the screening were age, sex, educational level, marital status, socioeconomic status, data on chronic diseases, and medications. A clinical assessment was conducted using the Montreal Cognitive Assessment (MoCA) test [24,25] to exclude participants with suspected cognitive impairment (ie, achieving a total MoCA score lower than 26 points). After qualification, the participants were randomly allocated to either the experimental or the control group. These participants were invited for a second visit, during which they completed a battery of tests for neuropsychological and psychosocial assessment and were trained on how to use the VR-HMD on their own.

#### Ethical Considerations

The protocol and the informed consent form (Multimedia Appendix 1) received approval from the Bioethical Committee of the MUL, Poland (RNN/222/21/KE). Each participant was introduced to the study by a research team member, who performed an initial demonstration of the equipment. The participants were given time to ask any remaining questions. Following this, if they agreed to take part, they signed a form giving their written informed consent (Multimedia Appendix 1).

All data collected during the study will be entered into a secure, password-protected electronic database (internal cloud service and protected from external access). The data set for statistical analysis was fully anonymized. Participants’ paper files will be stored in numerical order and in a secure place and manner. A coding system will be developed to ensure uniformity and consistency in categorizing variables. Each variable will be assigned a unique code that will be used throughout the study for data entry and analysis. Access to the data will be restricted to authorized personnel only. Data will be stored on a secure server with regular backups to prevent data loss. Personally identifiable information will be stored separately from the research data to maintain participant confidentiality.

In the conduct of this research, all human participants participated voluntarily and without the promise or receipt of financial compensation or any other form of remuneration.

